#### qPCR

4.7.2

In our study, qPCR will be done in 2 phases:

a) Pre-16S sequencing analysis

In this phase, qPCR will have 2 purposes: 1st, to confirm and further characterise the bacterial functionary groups in faeces evaluated by bacterial culture (providing the information of viable bacteria inside specific functionary group); and 2nd, to quantify pathogens/commensals in respiratory and intestinal system, known to be implicated in tumourigenesis/pro or anti-inflammatory reactions^[27–32]^ using specific primers.

The qPCR will provide information of absolute quantity of taxa/species of interest in each sample, which is information that cannot be obtained by sequencing (only relative abundance).

b) Post-16S analysis

In our study, the sequencing has the purpose of sample “screening”. It will give us an idea of the composition of the microbial communities from different sites and originating from different conditions (patient with tumours eligible for chemotherapy/surgery) based on minimum of 5000 reads. However, sequencing stays a technique to determine relative abundance. Therefore, once the overall composition of each sample is determined, we will proceed with:

1.quantification of the specific outer taxonomic units (OTUs)/taxa we determine as relevant in either relative or normalised abundance not analysed during pre-16S analyses2.enlarging the primer list specific for the new discovered OTUs of interest

The current list of primers optimised for our study is shown in Table 2. Each primer couple is tested for specificity on 60 referent species. The QPCR will be done using the Rotor-Gene Q machine (Qiagen). Additional primer couples will be tested and optimised if found necessary, as explained.

**Table 2 T2:**
[figure not shown]
The current list of qPCR primer couples.

### Statistical analysis plan

4.8

#### General information

4.8.1

This study is exploratory and main outcomes address the description of microbiota characteristics in lung cancer patients. Three microbiota are concerned (gut, lung, and saliva) and data are collected at different times in patients treated by neoadjuvant chemotherapy (group Pct-chir). For other patients (group Pchir), different microbiota are sampled at only 1 time point, at surgery.

In patients treated by chemotherapy, analysis of variations of microbiota induced by chemotherapy will be possible by evaluation of changes in proportions over time. On the other hand, the analysis of microbiota with/without previous chemotherapy will only be descriptive, as the design is not compatible with a non-biased comparison of both groups.

#### Sample size

4.8.2

The sample size calculation is based on the study of Montassier et al, 2015,^[53]^ where the abundance of the principal phylum *Firmicutes* in faecal microbiota decreased by approximately 30%, with an FDR-corrected *P*-value of .0002. Considering these results, 20 patients in the chemotherapy group should allow us to detect a similar variation in our samples, at least in the faecal microbiota. For group balance, the same sample size of 20 was retained for the surgery-only group.

#### Description of patients’ characteristics

4.8.3

Patients’ characteristics will be described using standard distribution parameters: counts, range, mean/median, confidence intervals, standard deviation/interquartile range for quantitative parameters and, for categorical ones, counts and frequencies. This description will also be made by treatment group (Pchir/Pct-chir).

#### Description of microbiota

4.8.4

Microbiota characteristics consist in several hierarchical steps including:

Phylum: 4 main phyla are found in both lung and intestinal microbiota (*Firmicutes*, *Bacteroidetes, Actinobacteria*, and *Proteobacteria*). *Firmicutes* are supposed to represent ∼80% of the intestinal microbiota biomass^[54]^ and ∼40% of the lung microbiota.^[55]^ The proportion of each component will be described by its proportion of the biomass in %.Main classes of bacteria per phylum: these classes gather bacteria that share important characteristics and functions (e.g. *Bacilli*, *Clostridia*, *Gammaproteobacteria,* etc.). Composition of the microbial communities from different sites and originating from different conditions will be quantified (alpha and beta diversity, relative proportions).Inside classes, description by order, family and genus level will be performed when contributory on a biological plan.

Heterogeneity between microbiota will be studied. The comparison of proportions of phyla, or by other taxonomic level will be performed to evaluate if specific adaptation characterises the 3 microbiota and their components. The ANOVA will be used to perform inter-patient comparisons. The FDR correction will be applied when analyses are conducted within phyla.

#### Comparison of microbiota before/after chemotherapy

4.8.5

This comparison will be performed for each site-specific microbiota. Proportions of main phyla will be compared using ANOVA (mixed model) to check if an independent chemo-effect can be objectivised, adjusting on patients and phyla (without FDR correction).

Comparisons of taxonomic levels below phylum before/after chemotherapy will be performed on relevant components with an FDR correction. These comparisons will be performed on both alpha and beta diversity. Univariate paired parametric or non-parametric tests (Student *t* test, Mann–Whitney *U* test, etc.) will be used here.

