
Therefore, to help to elucidate this new and extremely interesting field, we have decided to conduct a case-control observational study in patients with NSCLC. The study will include 2 groups of patients: 1st group Pchir, with patients eligible for treatment by surgery, and 2nd group Pct-chir, with patients eligible for a combined treatment consisting of neoadjuvant platinum-based chemotherapy followed by surgery.

The objectives of this study are:

(i)to characterise the gut, lung and upper airway microbiota in these patients;(ii)to evaluate the homogeneity/heterogeneity between different microbiota within the same subject/group of patients;(iii)to evaluate the impact of the microbiota composition on immune and inflammatory status of the patient (evaluated in the gut, blood, lung);(iv)to evaluate the effect of chemotherapy on the site-specific microbiota (UAs, lung, gut).

While group Pchir will have only 1 time point for sample collection, group Pct-chir will have multiple time points. The latter will enable follow-up on changes in microbiota and immune markers relative to the treatment progression.

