The strong point of this trial is that study participation does not modify the patient's standard care treatment in any way. Invasive intervention, such as sampling of the lung tissue, is done during operation on the lung already removed from the patient. The BALF sampling during operation is performed directly on the dissected lobe, posing no additional inconvenience for the patient and drastically minimising UAs contamination, which is an important advantage to this study's concept. Likewise, sampling of the BALF at CT1 for group Pct-chir is done in the scope of a standard care procedure by bronchoscopy and it is not imposed by the study. However, the latter is also an inconvenience because there will be patients from group Pct-chir who will not undergo bronchoscopy with BALF sampling since it is not prescribed by his/her physician. Another thing to consider is also the difference in sampling technique of BALF. Sampling of BALF at CT1 for group Pct-chir is done by bronchoscopy, while sampling during surgery is done directly on the excised lobe for both groups. Therefore, the 1t BALF has a higher risk of contamination by UAs, while the 2nd BALF (during operation) should have no UAs contamination and better represent luminal microbiota specific of the tumour lobe. This will be taken into account during data interpretation, and if necessary, each time point will be characterised for itself.

In conclusion, in the group Pct-chir, the effect of chemotherapy on the microbiota of saliva and faeces and immune parameters of blood and faeces will by systematically assessed. Chemotherapy's effect on immune parameters and microbiota in BALF will be assessed only if obtained data in quantity and quality will permit it (as explained above). When talking of lung tissue, “healthy” lung tissue, taken at distance from the tumour, will be considered as a control^[12]^ tissue for comparison with peritumoural and tumoural tissue, as well as with BALF. Also, characterisation will be done respective to the tumour type where possible (sufficient patient number with the same tumour type).

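### Change from CT1 to surgery in the chemotherapy group has no untreated time course beside it, so the plan can describe change over the chemotherapy period but cannot attribute it to chemotherapy

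*Protocol article*

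**What the plan says.** The Introduction sets as objective (iv) the evaluation of chemotherapy's effect on the microbiota of each site. Section 2.2 repeats this as secondary outcome (i). The sampling differs by group: "While group Pchir will have only 1 time point for sample collection, group Pct-chir will have multiple time points". Section 4.8.1 confirms that in Pchir "different microbiota are sampled at only 1 time point, at surgery".

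Three statements then give the within-group change a causal reading:

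- Section 4.8.1: "analysis of variations of microbiota induced by chemotherapy will be possible by evaluation of changes in proportions over time".
- Section 4.8.5: phylum proportions go into a mixed model, adjusted for patient and phylum, "to check if an independent chemo-effect can be objectivised".
- Section 2.5: "the effect of chemotherapy on the microbiota of saliva and faeces and immune parameters of blood and faeces will by systematically assessed".

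The caveats lie elsewhere. Section 4.8.1 says the comparison with and without previous chemotherapy "will only be descriptive, as the design is not compatible with a non-biased comparison of both groups". Section 2.5 warns about BALF, which is obtained by bronchoscopy at CT1 and from the excised lobe at surgery. Section 5.4 names the missing healthy control group as the main limitation. None of these qualifies the inference for saliva and faeces.

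**The concern.** Within Pct-chir every patient receives chemotherapy, and every later sample comes after it. Nothing planned shows how saliva or faecal microbiota would have moved over the same weeks without it. A patient term removes stable differences between patients, not change over time.

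The protocol itself supplies one competing cause. Section 3.1 expects some patients to change their diet during chemotherapy and notes that faecal microbiota responds to a diet change within days. Diet is recorded for seven days before each sample, but it is not among the adjustments in section 4.8.5.

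At stake is what the trial may conclude. A significant before/after difference would be reported as a chemotherapy effect when the design supports only a change over that period. A larger sample or FDR correction would not help, because the problem is bias and not precision or multiplicity.

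**Working it through.** **1. The plan's own figure.** Section 4.8.2 sets 20 patients in the chemotherapy group to detect a fall of about 30% in faecal Firmicutes. It states neither power nor the SD of paired differences, so 20 cannot be reproduced uniquely. As a plausibility check, a two-sided paired t test at 5% with n = 20 has 80% power for a mean change of 0.66 SD of the paired difference. Section 4.8.4 puts Firmicutes at about 80% of the gut microbiota, so a 30% relative fall is 0.30 × 80 = 24 points. Power is then at least 80% if that SD is no more than 24 / 0.66 ≈ 36 points. Twenty is plausible for detecting a change, but it says nothing about the cause.

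**2. The interval.** Section 2.5 gives about 3 weeks from CT1 to CT2 and about 1 month from CT2 to surgery: 21 + 30 = 51 days, and 51 / 7 ≈ 7 weeks.

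**3. What the contrast estimates.** Write the mean change from CT1 to a later sample as *c* + *d*, where *c* is the part due to chemotherapy and *d* is everything else that shifts over the same time.

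- CT1 to CT2 estimates *c*₁ + *d*₁.
- CT1 to surgery estimates *c*₂ + *d*₂.

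That is two observed means and four unknowns. Two things could separate them. The first is a slope before treatment, which needs at least two samples before chemotherapy; there is one. The second is repeated sampling of untreated patients; Pchir has one time point. Patient effects cancel in the difference and phylum terms do not vary with time, so neither adjustment isolates *c*.

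**4. Illustration of size.** The documents give no value for *d*. Assume *c* = 0 and a drift in the same direction across patients, with mean *g* in units of the SD of the paired difference. The probability that a paired t test rejects at two-sided 5% is

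P(|T| > t₀.₉₇₅,₁₉), with T noncentral t on 19 degrees of freedom and noncentrality *g*√20.

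| Assumed *g* | *g*√20 | P(reject), n = 20 |
|---|---|---|
| 0 | 0 | 0.05 |
| 0.2 | 0.89 | 0.14 |
| 0.3 | 1.34 | 0.25 |
| 0.5 | 2.24 | 0.56 |

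A simulation of 40,000 trials gave 0.249 at *g* = 0.3 and 0.563 at *g* = 0.5. With n = 200 and *g* = 0.3 the rate is 0.99, so a larger sample makes the misattribution more certain. In the same simulation, a comparison of changes against a hypothetical untreated group of 20 with the same drift rejected in about 5% of trials at each of the four drifts simulated (0, 0.3, 0.5 and 0.66). This shows that the missing piece is the untreated series. It does not show that Pchir could supply one.

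**The case against.** The strongest reply is that the term independent in section 4.8.5 is statistical: a period effect net of the listed factors, patient and phylum. That reading is fair for section 4.8.5 alone. It does not cover section 4.8.1, which describes the changes over time as caused by chemotherapy and sets this analysis against the between-group comparison, the one it concedes to be biased.

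Several other points stand and limit the concern:

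- The study is exploratory and the chemotherapy effect is a secondary outcome. That excuses imprecision, but not a causal label.
- The rapid faecal change in section 3.1 is tied to diet. A reader might infer from it that untreated microbiota drifts within days; the text does not say so. The diet records are a real mitigation, although they are outside the model and cannot stand in for an untreated series.
- Preparation for surgery can hardly explain the CT1 to CT2 change, which precedes surgery by about a month. Sampling close to admission (sections 3.2 and 3.4) limits its influence on the last sample too.
- A reader might extend the point to blood under objective (iv) and section 4.8.5. Both concern microbiota only, and section 2.5 shows that blood is not drawn at CT2.
- The ethics committee refused a control group because of invasive sampling. That explains why controls are absent, but a healthy group sampled once would not have closed this gap either.

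A second Pchir sample might look like the remedy. The documents do not support it. An early kit handed in at admission would break the 12-hour rule for faeces in section 3.4. The 1.5-month average follow-up in section 2.5 is not a sampling interval. Section 4.8.1 also calls the two groups unsuitable for unbiased comparison.

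**Conclusion.** The point holds as a matter of attribution. For saliva and faecal microbiota, the change from CT1 to CT2 to surgery mixes any chemotherapy effect with elapsed time and concurrent changes, including diet, and no planned analysis separates them. The plan can describe change over the chemotherapy period. It cannot establish that the change is an independent effect of chemotherapy or was induced by it.

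The 14% to 56% range rests on an assumed drift of 0.2 to 0.5 SD, consistent in direction across patients; random fluctuation would only widen the SD. It models an unadjusted paired t test at 5%, whereas the plan uses a mixed model for phyla and FDR-corrected tests below phylum. A reader might take the range as this trial's false-positive rate, but the documents support neither the drift sizes nor that test. A reader might also infer that the before/after analysis is worthless or that 20 patients is wrong. Neither follows: the data keep their descriptive value, and the sample size is neither confirmed nor refuted. This is a modest point in an exploratory study, but it changes what the trial may conclude.

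**What to change.** In objective (iv) of the Introduction, secondary outcome (i) in section 2.2, the concluding paragraph on Pct-chir in section 2.5, and sections 4.8.1 and 4.8.5, restate the target as change during the neoadjuvant chemotherapy period, and say that it is not attributable to chemotherapy alone. In section 5.4, add to the limitations, beside the missing healthy controls, that no untreated patients are sampled repeatedly and that only one sample precedes chemotherapy.

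No sample, visit, test or patient number changes. The cost is a more modest claim.

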#### Comparison of microbiota between the 2 treatment groups

4.8.6

These comparisons will use the same tests as in the previous paragraph, except tests will not be paired.

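### The pooled phylum model in section 4.8.5 tests the mean change over phyla, which barely responds to the Firmicutes fall the trial was sized on

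*Protocol article*

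**What the plan says.** Section 4.8.5 (before/after chemotherapy) states the phylum-level analysis in one sentence. The main-phylum proportions go into an ANOVA (mixed model) "to check if an independent chemo-effect can be objectivised, adjusting on patients and phyla (without FDR correction"). The univariate paired tests that follow in 4.8.5 are for taxonomic levels below phylum.

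Section 4.8.4 defines the response: "The proportion of each component will be described by its proportion of the biomass in" percent. It also says that "4 main phyla are found in both lung and intestinal microbiota" and that Firmicutes "are supposed to represent ∼80% of the intestinal microbiota biomass".

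Section 4.8.2 sizes the trial on one phylum. In the cited study, Firmicutes "in faecal microbiota decreased by approximately 30" percent, and from this the article concludes that "20 patients in the chemotherapy group should allow us to detect a similar variation in our samples". Section 2.2 makes the change in the Firmicutes share under chemotherapy secondary outcome (i)a.

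Section 4.8.6 (between treatment groups) adds: "These comparisons will use the same tests as in the previous paragraph, except tests will not be paired".

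**The concern.** Phylum can be an adjustment factor only if all phyla enter the same model. With patient and phylum as adjustments and no interaction, the chemotherapy term is one number: the change averaged over phyla. Shares of a whole offset each other, so a fall in one phylum is made up by rises in others and the average hardly moves. The effect of interest, a change that differs between phyla, goes into the residual.

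Section 4.8.5 is the only part of section 4.8 that specifies a before/after test at phylum level, and the trial was sized on a phylum-level change. A null result built into the model could be reported as absence of a chemotherapy effect.

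**Working it through.** **Inputs from the article.** Four main phyla; gut Firmicutes about 80% (4.8.4); a fall of about 30% and 20 patients (4.8.2); two-sided 0.05 (4.8.9). A relative fall of 30% from 80% is 80 × 0.30 = 24 points, that is, 80% to 56%.

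**Assumed.** The article gives no SD of the change and no target power, so both the scatter and the other phyla's shares are assumptions, shown as ranges.

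**The plan's own figure.** Without an SD or a power, 20 cannot be reproduced; only its plausibility can be checked. A paired t test with n = 20 has 80% power for a standardised change of 0.66 and 90% for 0.764. A 24-point fall is therefore detectable if the SD of the paired change is at most about 24/0.66 ≈ 36 points (80% power) or 24/0.764 ≈ 31 points (90%). Twenty is plausible for a paired test on Firmicutes itself.

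**The tested term.** The model as written is: share = mean + patient + phylum + δ × time + error. With balanced data, the estimate of δ is the average over patients of (S_after − S_before)/4, where S is the sum of the four phylum shares in a sample.

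- If S = 100 in every sample, δ = (100 − 100)/4 = 0, whatever the SD. Example: Firmicutes 80 to 56, the others 12 to 30, 4 to 5 and 4 to 9. The changes are −24 + 18 + 1 + 5 = 0.
- If other phyla hold a share O, then S = 100 − O and δ = −(change in O)/4. A rise from 2% to 10% gives −2.0 points, and from 5% to 15% gives −2.5 points. The Firmicutes change does not enter except through O.

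**Simulation.** 20 patients, Dirichlet compositions, 2,000 trials per scenario, Firmicutes 80% to 56%. Rows with other phyla use a paired-change SD of about 14 points.

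| Scenario | Power, pooled chemotherapy term | Power, paired Firmicutes test |
|---|---|---|
| Four phyla sum to 100%, SD about 9 to 19 | 0% | about 100% |
| Four phyla sum to 100%, SD about 26 | 0% | 96.5% |
| Others constant at 2%, 5% or 10% | 0% | about 100% |
| Others 2% to 5% | 0% | about 100% |
| Others 2% to 10% | 0.4% | about 100% |
| Others 5% to 15% | 13% | about 100% |
| Others 2% to 26% (the whole loss leaves the four phyla) | about 100% | about 100% |

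The 5%-to-15% figure depends on the scatter. It is about 5% at an SD near 17 points, lower with wider scatter and higher with tighter data. At the widest scatter tried (SD about 32 points), the paired Firmicutes test still had about 88 to 89%.

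**Direct fit.** A mixed model with random patient and fixed phylum and time, on one closed data set, gave a time effect of 0.0 (p = 1.0). In the same data Firmicutes fell by 24.3 points (p about 1e-15).

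**The obvious repair.** A plain time-by-phylum F test on raw proportions had 99% power at an SD of about 26 points. However, with no chemotherapy effect it rejected in about 10 to 11% of trials at nominal 5%, because it ignores the correlation between phyla. The paired Firmicutes test rejected in about 5%.

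**The case against.** The article gives no formula, and a fuller plan may contain a chemotherapy-by-phylum term. The remark about FDR could also suggest several phylum comparisons rather than one. This stands as a caution, but what is written describes phylum as an adjustment. If an interaction is meant, the sentence misstates the model and still needs correcting.

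A reader might infer that the test is zero whatever happens to the flora. The article does not support that. It speaks of main phyla and never says that they make up 100%, so a large enough move into or out of the other phyla would register. What would register is that move, not the Firmicutes fall.

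A reader might also infer that the trial would miss the Firmicutes shift altogether. It would not: section 4.7.1 plans comparisons of OTU frequencies at phylum level and tests on distance matrices, and section 4.8.4 describes each phylum's share.

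Nor is it established that section 4.8.6 has the same defect. The tests it makes unpaired may be the univariate ones, which are free of the problem, and section 4.8.1 says the comparison with and without chemotherapy will only be descriptive.

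Finally, the study is exploratory and this is a secondary outcome. That limits the consequences but does not rescue a test that cannot respond to its target.

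**Conclusion.** The point holds for the pooled model in 4.8.5 as written. Its chemotherapy term is exactly zero if the four phyla sum to 100%, and otherwise minus one quarter of the change in the remaining share. Power for the 80% to 56% fall is 0% in the closed case and when the other phyla are stable. It becomes substantial only when much of the loss goes to phyla outside the four, or when a moderate shift of that kind meets very tight data.

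The algebra needs only the additive reading and no variance. The power figures rest on assumed scatter and Dirichlet compositions. The sample size of 20 is not shown to be inadequate, since a direct paired Firmicutes test could use it well. The model cannot serve secondary outcome (i)a and should be corrected before analysis.

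**What to change.** In 4.8.5, replace the pooled additive model with one model per phylum and site, for sites with samples before and after chemotherapy. Put the proportion on a logit or centred-log-ratio scale, with time as a fixed effect and patient as a random effect, or use a paired test per phylum. Transforming alone does not help: centred log-ratios sum to zero within a sample, so the phyla must also be analysed separately.

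Report faecal Firmicutes from CT1 to surgery as the test that matches the sample-size rationale, and apply FDR correction to the other phylum tests.

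If a time-by-phylum interaction is preferred, it must allow for the correlation between phyla (log-ratio or multivariate), since the plain F test on raw proportions does not hold its level.

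In 4.8.6, state which tests are reused. If the pooled phylum model is meant, make the same change there and keep the comparison descriptive, as 4.8.1 says.

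The cost is a few sentences, with no new data or patients. The downside is that phylum p-values other than faecal Firmicutes become FDR-adjusted.

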#### The 16S rRNA gene sequencing

4.7.1

The genomic DNA from saliva, faeces, BALF, “healthy” lung, peritumoural and tumoural tissue, and negative controls will be analysed by sequencing of the bacterial 16S rRNA gene by DNAVision, Belgium, using Illumina MiSeq technology. After PCR amplification of the targeted region V3–V4, libraries will be indexed using the NEXTERA XT Index kit V2. The sequencing is carried out in paired-end sequencing (2 × 250 bp) by targeting an average of 10,000 reads per sample. Software used for bioinformatic analysis will be QIIME (Quantitative Insights Into Microbial Ecology), with a cut-off value of 5000 reads per sample for analysis. For each sample the following will be determined:

a)alpha and beta diversity,b)comparison of alpha diversities based on a 2-sample *t* test using non-parametric (Monte Carlo) method,c)statistical significance of sample groupings using distance matrices (Adonis method),d)comparison of OTU frequencies across sample groups (comparison is performed at OTU, Phylum, Class, Order, Family and Genus level)

Multiple comparisons will be realised, both between different grouping criteria and between samples.

Considering the low taxonomic levels (Species), sequencing is best used as an indicative tool for further analyses by qPCR.

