#### Complementary analyses

4.8.9

Complementary analyses will be performed if particular biological issues can be better described.

All statistical analyses will be performed using R-software version 3.5.0 or later (R-Project, GNU GPL). Tests will be 2-sided and the significance threshold is set at 0.05, after FDR correction where needed (as for the analyses concerning taxonomic ranks below phylum). Data may be missing due to possible loss of follow-up between inclusion and end of study. A description of the missing data and associated reasons will be given.

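### Section 4.8.5 prescribes paired before/after tests but names the unpaired Mann–Whitney U test as the rank example, and it assigns univariate paired tests to beta diversity

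*Protocol article*

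**What the plan says.** Section 4.8.5 of the protocol article treats the before/after comparison in two layers.

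- **Phyla:** "Proportions of main phyla will be compared using ANOVA (mixed model) to check if an independent chemo-effect can be objectivised, adjusting on patients and phyla".
- **Lower taxonomic levels:** "Comparisons of taxonomic levels below phylum before/after chemotherapy will be performed on relevant components with an FDR correction". The section then adds "These comparisons will be performed on both alpha and beta diversity", and gives the method as "Univariate paired parametric or non-parametric tests (Student *t* test, Mann–Whitney *U* test, etc.) will be used here".

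Section 4.8.6, on the two treatment groups, refers back to this: "These comparisons will use the same tests as in the previous paragraph, except tests will not be paired".

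Two other places bear on the point. The list of sequencing analyses in section 4.7.1 includes "statistical significance of sample groupings using distance matrices (Adonis method"), which section 4.8.5 does not mention. Section 4.8.9 sets the error rate: "Tests will be 2-sided and the significance threshold is set at 0.05, after FDR correction where needed".

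**The concern.** There are two separate faults in the wording.

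**The rank test.** Mann–Whitney U compares two independent samples. It takes no account of which before value belongs to which after value. It is nevertheless the only rank test named in a sentence about paired tests. An analyst who takes the non-parametric branch and follows the test name would run an unpaired test on paired data.

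**Beta diversity.** A univariate paired test needs one number per patient before treatment and one after. Beta diversity is a dissimilarity between two samples, so it supplies no such pair of numbers unless a per-sample score is derived from it (an ordination axis, for example). The article defines none. Section 4.7.1 names a distance-based method and section 4.8.5 names univariate tests, and neither refers to the other.

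At stake are the below-phylum chemotherapy comparisons. Section 4.8.1 makes the comparison of patients with and without chemotherapy descriptive only and looks to changes over time within the chemotherapy group. The change in genera is one of the secondary outcomes in section 2.2. The planned group is 20 patients, and fewer BALF pairs are likely because bronchoscopy before the first cycle is optional (section 2.5).

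**Working it through.** **1. What the text settles.** Section 4.8.5 says the tests are paired. Section 4.8.6 reuses them, "except tests will not be paired". Pairing is therefore intended in 4.8.5, and the test name is what conflicts with it.

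**2. Inputs from the document.** Planned chemotherapy group n = 20 (section 4.8.2); two-sided 0.05 (section 4.8.9). The document gives no power, no SD of change and no within-patient correlation ρ, so its sample size cannot be reproduced.

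**3. Assumed inputs.** Bivariate-normal before/after values with equal variances; ρ from 0 to 0.7; standardised paired effect dz = mean change / SD of change = 0.66, the value at which a paired t test on 20 pairs has about 80% power. No FDR step.

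**4. Why ρ drives the answer.** An unpaired test takes the variance of the mean difference to be 2σ²/n. With pairing it is 2σ²(1−ρ)/n. In normal approximation the nominal cut-off of 1.96 therefore acts like 1.96/√(1−ρ), against an expected signal of dz·√n = 0.66 × √20 = 2.95.

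- ρ = 0.5: cut-off 1.96/√0.5 = 2.77; power ≈ Φ(2.95 − 2.77) = Φ(0.18) = 57%; true type I error ≈ 2 × [1 − Φ(2.77)] = 0.6%.
- ρ = 0.7: cut-off 1.96/√0.3 = 3.58; power ≈ Φ(2.95 − 3.58) = Φ(−0.63) = 26%; true type I error ≈ 0.03%.

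**5. Simulation of the two rank tests** (20 pairs, dz = 0.66). Repeat runs of 4000 data sets per setting agree with the power figures to within about 2 percentage points.

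| ρ | Signed-rank power | Mann–Whitney power | Mann–Whitney type I error |
|---|---|---|---|
| 0 | 78% | 80% | 5.0% |
| 0.2 | 79% | 73% | 3.1% |
| 0.3 | 77% | 67% | 1.8% |
| 0.5 | 79% | 53% | 0.9% |
| 0.7 | 78% | 26% | 0.1% |

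The signed-rank test stays near 5% under the null. At ρ = −0.2 the Mann–Whitney type I error is 8.2%, so the departure is conservative only for positive correlation.

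**6. Dependence on effect size.** With a shift of 1.3 SD of the measurement itself, both tests have at least 96% power at ρ = 0, 0.3, 0.5 and 0.7.

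**7. Adding an FDR step.** This needs further assumptions: 50 independent normal taxa, 10 of them shifted, Benjamini–Hochberg at 5%, 300 runs. At dz = 0.66 the share of true shifts found, signed-rank v Mann–Whitney, is about 38% v 17% at ρ = 0.3 and 41% v 5% at ρ = 0.5. At dz = 1.0 and ρ = 0.5 it is 91% v 56%. At ρ = 0 nothing is lost at either effect size. This shows the direction only, since the article gives neither the number of taxa nor how many are expected to change.

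**The case against.** A reader might infer that the plan drops the pairing and gives up much of its power. The document does not support that. The governing word in the sentence is paired, section 4.8.6 confirms it, the list of tests is open-ended, and a paired Student t test is allowed. An analyst who follows the adjective will look for the signed-rank test. Power is lost only if Mann–Whitney U is actually run, and then only to an extent set by a correlation and an effect size that appear nowhere in the article. At zero correlation nothing is lost, and for large effects little is. The simulated data are also normal, while the rank branch would be chosen for data that are not.

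On beta diversity, one might infer that pairwise distances will be analysed as if independent, or that the plan has no valid method. Neither follows. No sentence says the distances will be treated that way, section 4.7.1 already names Adonis, and a derived per-sample score could be tested in pairs.

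The reach is limited as well. The study is declared exploratory, the chemotherapy effect is a secondary outcome, and the main-phylum comparison keeps the pairing through a mixed model adjusted on patients. That comparison includes Firmicutes, on which the 20 patients rest.

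All of this stands as a limit on size and severity. It does not remove the two faults: the only rank test named is not a paired test, and section 4.8.5 gives beta diversity a class of tests that does not fit it without a further definition.

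**Conclusion.** The point holds as a contradiction within section 4.8.5 and a mismatch between that section and 4.7.1. It does not hold as a demonstrated loss of power. If the named rank test were run on 20 pairs with dz 0.66, the change in power against the signed-rank test would be a gain of about 2 points at ρ = 0 and losses of about 6 points at 0.2, 10 at 0.3, 26 at 0.5 and 52 at 0.7. True type I error would fall from about 5% to about 0.1% over that range. These figures rest on an assumed normal model, an assumed effect and an assumed correlation, without FDR. The phylum-level analysis is untouched. The affected comparisons are secondary and exploratory, so this is a low-cost correction and not a condition for the study to proceed.

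**What to change.** In section 4.8.5, replace the Mann–Whitney U test with the Wilcoxon signed-rank test. In section 4.8.6, name Mann–Whitney U explicitly for the unpaired comparisons, because the reference back to 4.8.5 would no longer lead to it. Limit the univariate paired tests to alpha diversity and taxon abundances. For before/after beta diversity, refer to the Adonis method of section 4.7.1 and state that permutations are restricted within patient, since that section states no such restriction.

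The cost is a sentence or two in the analysis section, with no change to data, samples or budget. It is best made before the before/after data are analysed, so that the choice of test cannot follow the results.
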